### Limitations

Operational challenges are numerous and are linked to the relationship with MWSW communities and their perception of the intervention, mobility of the participants, stigmatization and racism that they could face from institutions, decrease in preventive actions, and modification of the type of sex work due to health measures or restrictions linked to the COVID-19 pandemic. Documenting all these logistic and operational aspects should enable gathering of crucial information regarding the potential transferability of the intervention.

Regarding the FASSETS methodology of evaluation, we were unable to use a control group or a stepped wedge method because of ethical problems (benefit to participate) and the difficulty to implement empowerment in a sequential and reproducible way. However, exhaustive local data from all screening and delivery PrEP centers in Marseille are available for investigators at the beginning and at the end of the study and will permit them to evaluate, through pre- and postintervention comparisons and those between participants and nonparticipants, the access and adherence to PrEP among MWSWs.

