Previous studies on HIV prevention programs have specifically targeted WSWs, and PrEP has emerged as a potentially effective option for HIV prevention in this population, with most studies being performed in transitional countries [12]. PrEP is highly effective in reducing HIV incidence in this population with appropriate individual compliance [13]. Unfortunately, 2 PrEP trials among cisgender women in Africa were stopped early due to suboptimal adherence [14,15]. The subject of adherence and its determinants is of tremendous importance in this population [12]. As with HIV risk factors, determinants of PrEP use in WSWs arise from multiple social and biological factors [9,14,16]. MWSWs face structural factors associated with a precarious immigration status, migration, and occupation-related marginalization [11]. A systematic review among WSWs has stressed the need for comprehensive care in order to increase the use of and adherence to PrEP [12,17]. However, few studies have investigated how to implement community-based interventions to promote PrEP access and health equity within this vulnerable population [11]. Indeed, there is a need to develop interventions with a holistic approach, including specific clinics and social services [12,18]. Another key element is to implement a prevention intervention based on community empowerment, in which MWSWs take collective ownership of knowledge of and resources about sexual health [19].

In France, as in other European countries and the United States, women represent a minority of PrEP users (less than 3%) [20-22]. Marseille is France’s second largest city and one of the poorest (with 200,000 people living with less than €1000 [US $1086.26] per month) located on the Mediterranean coast [23]. In 2018, overall 12% of Marseille’s population (192,330 inhabitants) was born abroad and statistically considered a migrant population with 28% of them born in northern Africa and 14% of them born in sub-Saharan Africa [24]. These figures do not take into account undocumented migrants. Among 2197 people consulting for PrEP at the 10 medical centers for sexual health and prevention (managed by the departmental council of the Bouches du Rhône—an area of Marseilles and its suburbs) between 2016 and 2022, only 7 were MWSWs [25].

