### Objectives of the Different Phases of the Study

Phase 1 will describe the determinants of PrEP uptake in MWSWs with a multilevel approach including individual, collective, and institutional analysis.

Phase 2 will determine the size of the MWSW population in Marseille.

Phase 3 will describe attitudes, knowledge, and practices of sexual and reproductive health (SRH) among MWSWs, health care pathways and mobility, testing for sexually transmitted infections, and prevalence and frequency of screening in the MWSW population at month 0 and their evolution during follow-up.

Phase 4’s primary objective is to analyze access to PrEP and retention in care through a community empowerment follow-up of MWSWs. Secondary objectives will be to document individual and collective empowerment tools for MWSWs and to describe CHW interventions for MWSWs.

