### Training of Community Health Workers and Intervention Implementers

The CHWs will be members of the communities to which the recruited MWSWs belong. They will be able to improve recruitment, accurately monitor the correct understanding of the questionnaires, and conduct and ensure participation in empowerment, prevention, and screening interventions. They will provide information about PrEP and assist with care and follow-up for participants who wish to receive the treatment. They will be uniformly trained to conduct the survey using a structured interview. All actions (type, date, and public) taken by the CHWs with MWSW participants (eg, access to care, prevention, and assistance in accessing social insurance) will be also collected.

The CHWs will be responsible for health education and individual and collective empowerment actions. They will receive rigorous prejob training and assessment, which include PrEP use and sexual health prevention and care, by caregivers (infectious disease physicians) and nationally recognized community-based NGOs working in the field of HIV prevention (including AIDES, Planning familial, and COREVIH [COordination REgionale de lute contre le Virus de l’Immunodéficience Humaine]). The training program will be conducted with the entire CHW group and will also include individualized follow-up. All CHWs will have a discussion platform via a social network to obtain real-time responses from physicians. Information or prevention tools, adapted to the MWSW populations, will be made available to the CHWs by the NGO’s partners. Posttraining mentorship, supervision, and monitoring with regular training will take place every 3 months by the investigating physicians. CHWs’ course evaluation feedback and posttraining monitoring visits will be provided by the study coordinator. Finally, a follow-up and psychological support will be set up to support the CHWs in their work with this vulnerable population.

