### Data Collection

Upon enrollment and at months 3, 6, and 12, participants will be asked to complete a structured survey administered by a CHW. The survey will include questions regarding network size for RDS weighting. These will include questions about the token given at the time of data capture. Individual data including sociodemographic characteristics; sexual practices; knowledge and behavior; HIV testing history; medical history; PrEP knowledge, adherence, and compliance; contraception; drug and alcohol use; mental health (including Perceived Stress Scale-10 scores); quality of life; literacy; social support; being subjected to racism; stigmatization or violence during the past 12 months; and mobility will be collected. Other more structural determinants will be collected as follows: residence permits, health insurance, housing conditions, and food security (Table 1). Indeed, such structural determinants are previously described to have a significant impact on health care access among sex workers [42]. The semistructured questionnaire will explore the barriers and levers to accessing PrEP among MWSWs. The instrument or interview guide will attempt to understand how PrEP fits into women’s needs, care pathways, and mobility. Representation of MWSWs’ PrEP uptake among caregivers and which mechanisms are (or are not) implemented by social institutions to facilitate access to prevention and care for MWSWs (Table 1).

Type, objective, and number of actions of mediation in terms of prevention, support, or access to health care or social services will be self-reported by CHWs.

CHWs will use encrypted and secure survey software to report the MWSWs’ responses to the questionnaires and to monitor their actions of mediation. All electronic questionnaires will be forwarded to a database that is managed and hosted by SESSTIM (Inserm laboratory in Marseille). Each staff member will have a secure individual account.

Databases of all NGOs and institutional screening and PrEP centers of Marseille will be retrospectively analyzed to describe the HIV status and to assess PrEP characteristics among migrants and women in Marseille.

**Table 1 table1:** Data collection tools and timing.

Method	Timing	Population	Data collected

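### The Limitations section overstates what the centre-record comparison can show: no denominator is assigned to nonparticipants, and the two contrasts, listed separately, handle neither trend nor self-selection

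*Protocol article*

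**What the plan says.** The Introduction sets the aim of evaluating how effective the community empowerment intervention is in improving PrEP use, in a cohort of 150 migrant women sex workers (MWSWs).

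Limitations states "we were unable to use a control group or a stepped wedge method because of ethical problems (benefit to participate", and adds that empowerment is hard to deliver in a sequential, reproducible way. It then offers a substitute: "exhaustive local data from all screening and delivery PrEP centers in Marseille are available for investigators at the beginning and at the end". These data are said to permit an evaluation "through pre- and postintervention comparisons and those between participants and nonparticipants, the access and adherence to PrEP among MWSWs". No caveat follows.

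Data Collection describes what appear to be the same databases as to be "retrospectively analyzed to describe the HIV status and to assess PrEP characteristics among migrants and women in Marseille"; sex work is not named there. Objectives of the Different Phases of the Study says "Phase 2 will determine the size of the MWSW population in Marseille", and the phase 2 section gives the capture-recapture formula. Nothing in the article connects that estimate to the centre-record comparison.

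Data Analysis names chi-square or Fisher tests, Student or Wilcoxon tests, logistic regression and a log-rank test, at P≤.05.

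**The concern.** The issue is an affirmative statement that the two named comparisons do not support, not the lack of a control group, which is disclosed and explained.

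- **Denominator.** A nonparticipant who never reaches a centre leaves no record. Participants have a known denominator of about 150. For nonparticipants the article assigns none, so access cannot be expressed as a proportion on the same footing.
- **Trend.** A before/after contrast alone credits any change over the period to the programme. The same section mentions reduced preventive actions and changed sex work under COVID-19 restrictions, so such change is plausible.
- **Selection.** Participants come through peer recruitment with food coupons and agree to be followed. They may differ from nonparticipants in readiness to seek care. A participant/nonparticipant contrast alone cannot separate this from the intervention.
- **Adherence.** It exists only among women who started PrEP, and starting PrEP is what the intervention is meant to change. The users in the two groups are therefore selected differently.

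At stake is whether an observed difference would be reported as an effect of the programme when it is an association of unknown origin.

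**Working it through.** The article gives no power, effect size or target difference for the 150, so there is no sample-size figure to reproduce. Population size N, number of tokens n1, user counts and trend multipliers below are assumptions. From the article come 150 participants (also used as n2), N = n1×n2/m, and 7 of 2197.

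**1. What the background figure is.** The Introduction reports that among 2197 people consulting for PrEP at 10 departmental centres "between 2016 and 2022, only 7 were MWSWs". 7/2197 = 0.32% (exact 95% CI 0.13% to 0.66%). This is a share of PrEP consultants, not of MWSWs, so it is not an uptake rate. As a count it is 7/7 = 1.0 to 7/6 = 1.2 women per year.

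**2. How far the denominator drives the result.** Assume 8 users among 150 participants (5.3%) and 7 among N − 150 nonparticipants.

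| Assumed N | Nonparticipant rate | Ratio of rates | Fisher p |
|---|---|---|---|
| 300 | 7/150 = 4.7% | 1.1 | 1.0 |
| 500 | 7/350 = 2.0% | 2.7 | 0.08 |
| 1000 | 7/850 = 0.8% | 6.5 | 0.0005 |

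The same user counts run from no difference to a strong one.

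**3. Can phase 2 supply the denominator?** Use the Chapman form, N̂ = (n1+1)(n2+1)/(m+1) − 1, with variance (n1+1)(n2+1)(n1−m)(n2−m)/[(m+1)²(m+2)]. With n2 = 150, n1 = 200 and true N = 1000, the expected overlap is m = 200×150/1000 = 30. This gives N̂ = 978, SE = 142, 95% CI 700 to 1256, and a nonparticipant denominator of 550 to 1106.

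| True N | n1 | m | 95% CI for N − 150 | Ratio of rates for 8/150 against 7 |
|---|---|---|---|---|
| 500 | 200 | 60 | 267 to 426 | 2.0 to 3.2 |
| 1000 | 200 | 30 | 550 to 1106 | 4.2 to 8.4 |
| 2000 | 100 | 7.5 | 583 to 2704 | 4.4 to 20.6 |

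The last column carries only the denominator's uncertainty, with user counts held fixed. A denominator can be had, but it is imprecise when the overlap is small.

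**4. How much trend could explain.** This is illustrative only, because step 1 is not the planned baseline. Expected users among 150 in 12 months = (7/years)×(150/N)×multiplier. With no trend this is 0.07 (N = 2000, 7 years) to 0.58 (N = 300, 6 years). With a tenfold rise it is 0.75 to 5.8, and the smallest count with one-sided Poisson p≤0.025 is then 4 to 12. Trend could explain a small rise but not easily a large one.

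**5. Sensitivity of a plain before/after test, again illustrative.** Against 7 in 7 years, 4 users in one year give an upper-tail exact binomial p of 0.039 (share 1/8). Doubling gives 0.078, and a 6-year window gives 0.06. Five users give 0.011 and 0.02 upper-tail for 7 and 6 years. Very few users sit near the threshold whatever their cause.

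**The case against.** Several stronger readings are tempting, and the article does not support them.

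- A reader might infer that nonparticipants have no denominator at all. Phase 2 estimates the whole MWSW population, so N minus about 150 can be derived. What is missing is the link.
- A reader might infer that the design cannot control for trend, or can never show a rise in access. Beginning and end data on both groups could support a difference-in-differences, and a large rise from about one case a year would be hard to ascribe to trend.
- A reader might take 2016-2022 as the pre-period and object that it runs into recruitment. That figure is background from 10 centres; Limitations refers to all centres, at the beginning and end of the study.
- A reader might call these records the only support for effectiveness. Phase 4 outcomes before and after, the cohort surveys, the retention analysis and the qualitative work also bear on it.
- A reader might infer that participants are measured by questionnaire and nonparticipants by records. The surveys are indeed administered by community health workers, and "The CHWs will be responsible for health education and individual and collective empowerment actions". But Limitations names centre data as the source for this comparison, so the asymmetry is conjecture.

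It is also fair that an article may leave the estimator to a fuller document, so the lack of a named model is not the finding. What still stands is the unqualified promise built on two separate contrasts, with selection into the cohort not acknowledged.

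**Conclusion.** The concern holds in this form: Limitations claims more for the centre-record comparison than the two contrasts, as described, can deliver. PrEP access among nonparticipants has no assigned denominator, and with identical assumed user counts that choice alone moves p from 1.0 to 0.0005. Neither contrast by itself handles secular or post-COVID change or self-selection. The adherence comparison conditions on a result of the intervention.

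The sizes rest on assumed N, n1, user counts and trend multipliers. The p values built on 7 of 2197 are illustrations, not forecasts of a planned test. The study remains useful; the wording and the analysis of this comparison should change before effectiveness is claimed.

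**What to change.** 1. Measure PrEP start and persistence from the same centre records in both groups, flagging participants where consent allows. State how MWSWs are identified in those records.
2. Use the phase 2 estimate minus participants as the nonparticipant denominator, and carry its confidence interval into the comparison.
3. Define the pre-period as ending before recruitment opened on March 1, 2022.
4. Replace the two contrasts with one aggregated before/after-by-group (difference-in-differences) comparison, with other migrant women at the same centres as the comparison series. Data Collection already plans that "Databases of all NGOs and institutional screening and PrEP centers of Marseille will be retrospectively analyzed". A quarterly interrupted time series is not advisable: about one case a year is 0.25 per quarter, and March 2022 to September 2023 gives only about six quarters.
5. Report persistence over all eligible women, not adherence among users only.
6. State that selection into the cohort remains, and limit the conclusion to association.

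**Cost.** More analysis work and a more cautious claim. The denominator will be imprecise if the capture-recapture overlap is small. Because recruitment has already begun, flagging may need fresh consent from a mobile, stigmatised population, so it may be incomplete.

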### Conclusions

The FASSETS intervention aims to understand whether the implementation of a specific community accompaniment for MWSWs regarding PrEP use with an adapted follow-up and wide access to health care and social services are sufficient to improve the uptake of PrEP in this vulnerable population.

## Abbreviations

CHW: community health worker
FASSETS: Favoriser l’Accès à la Santé Sexuelle des Travailleuses du Sexe
MWSW: migrant women sex worker
NGO: nongovernmental organization
PrEP: pre-exposure prophylaxis
RDS: respondent-driven sampling
SRH: sexual and reproductive health
WSW: woman sex worker
